#### Awareness creation and community mobilization in the intervention arm

Recruitment will be done via media advertisements, posters, billboards, and community awareness programs targeting all eligible women (women between 40–70 years) to participate in screening at designated PHCs.

Radio jingles in English and Yoruba, the local language in the study area, will be aired on the three major radio stations that cover the LGAs. This will be done twice daily for two weeks before the launch of the program and weekly subsequently, spanning the entire period of the study. A fifteen-minute twice-weekly local television program will also be broadcasted for two weeks before the commencement of the program. The aim of this is to sensitize people to the nature of the disease, remedy inaccurate notions about the disease, and highlight the benefits of screening. This will be followed by short weekly television advertorials updating people about the program and inviting women who are yet to be screened.

Awareness programs in the form of town hall meetings will be held quarterly in various districts across the LGAs. This will feature talks by breast cancer survivors, key opinion leaders in the LGA, and medical personnel. The awareness programs will utilize the health belief model constructs, which address the various issues associated with behaviour change.

Handbills and educational materials detailing the nature of the program, as well as educational materials about breast cancer and instructional details on breast examination will be distributed to women at strategic locations, such as markets and places of worship.

#### Screening and diagnostic evaluation schedule in the intervention arm

In the intervention arm, consecutive consenting asymptomatic (40–70 years) and symptomatic (30–70 years) women will undergo screening and diagnostic evaluations respectively. Asymptomatic women (age 40–70 years) presenting for screening at designated PHCs will be evaluated by trained CHNs. Evaluation will entail a focused breast history, CBE, and iBE. Women with positive findings on CBE or iBE will be scheduled for another visit to have breast imaging and if indicated a breast biopsy. Women with negative findings on CBE and iBE will be scheduled for a similar repeat annual evaluation. Women will, however, be told to return at any time if any abnormality is noticed before their scheduled visit. Every woman who is screened will be given a breast health card (pink card) containing her name, contact information, a summary of findings on evaluation, and the date of the next examination. A duplicate copy of the breast card will be kept at the health centre for reference and follow-up. In addition to the breast health card, a detailed record of CBE and iBE findings for each patient will be kept by the PHC Nurse.

Symptomatic women (age 30–70 years) without an obvious lesion will be evaluated like the asymptomatic population, with focused breast history, CBE, and iBE. Those with positive findings will progress to imaging while those with negative findings will be scheduled for repeat evaluation on a short-term basis (one month). If symptoms persist at the time of the next evaluation, they will progress to imaging regardless of CBE and iBE findings.

Symptomatic women (age 30–70 years) with obvious breast lesion(s) will undergo focused breast history and CBE examination and will be scheduled to have imaging evaluation and breast biopsy if indicated (Fig 3).

**Fig 3 pone.0284341.g003:**
[figure not shown]
Patients’ navigation pathway from screening to treatment in the intervention community.

#### Evaluation of patients with positive findings in the intervention arm

Women with positive CBE or iBE findings will be scheduled for imaging, which will be conducted by the Radiologist and mammography Technologist from OAUTHC who will visit the LGA with mobile ultrasound machines and a mobile 2D digital mammography unit once a month. The 2D mobile digital mammography machine is a General Electric (GE) dedicated mammography computed radiography system secured from Lilly Women’s Health, a non-Governmental Organization in Lagos State, South-west Nigeria, which is being rented to us for the proposed two-year study period. The mobile ultrasound machines are four mHealth ultrasound tablets available in the breast unit of the Department of Radiology, OAUTHC which were utilized for a just-completed study funded under the R21 category of National Institute of Health (NIH) “Tablet-based mobile Health ultrasound for point-of-care breast cancer diagnosis in Nigeria (1R21CA239784-01)”.

Patients from all the PHCs will be seen at a central location in the LGA. Patients with suspicious findings on imaging will undergo an ultrasound-guided core needle breast biopsy on the same day. Biopsy specimens will be fixed in 10% neutral buffered formalin immediately and transported to OAUTHC the same day for processing and pathology interpretation.

### Patient navigation and follow-up in the intervention arm

Patients with histologically confirmed breast cancer will be scheduled to visit the next available breast clinic at OAUTHC. Navigation to the breast clinic will be facilitated by the CHNs after the Radiologists have communicated the biopsy results to both the patient and the nurse (Fig 3). The CHNs will also check in with the patients regularly on weekly basis through phone calls and/or home visits to ensure they comply with their appointments and follow treatment recommendations. Each patient will have a Case Report Form (CRF) (S4 File) which contains the socio-demographic and clinical data; CBE, iBE, and imaging (ultrasound and mammography) findings; pathology diagnosis (histopathology and immunohistochemistry) and treatment data. The socio-demographic and clinical data, CBE, and iBE sections of the CRF will be filled out for the study participants by the trained CHNs while the imaging, pathology, and treatment sections of the CRF will be filled out by the research study assistants (RSAs). The filled CRFs at the three PHCs will be collated and transferred to OAUTHC by the RSAs who visit the PHCs on weekly basis to monitor recruitment activities and collect paper data records for upload to REDCap in OAUTHC.

#### Control arm

The control LGA is about 4 kilometers from OAUTHC which is the referral tertiary hospital in this study. There are radiological (including ultrasound, mammography, computerized tomography, and magnetic resonance imaging services), pathological and surgical specialty services for breast cancer within OAUTHC which is also the primary institution of the study’s principal and co-investigators in Nigeria. In the control LGA, awareness creation will follow a similar procedure as outlined above for the intervention LGA. No other intervention will take place in the control arm. Women will not be invited to participate in a screening program and there is no community-based imaging, biopsy, or navigation. Women are expected to present to the PHCs if they have breast complaints which is a routine practice. Management of patients with breast-related complaints will be based on the current standard of care which is a review by the CHNs who refer or clinically manage otherwise based on his/her assessment. Twice a month, research staff will visit the selected PHCs in the control LGA to obtain data on the number and records of breast-related cases seen at the PHCs and those referred to OAUTHC. Patients referred to OAUTHC for suspicion of breast cancer will be tracked to determine the stage at diagnosis and the timelines from presentation at the PHC to eventual treatment at OAUTHC. In addition, patients presenting directly to OAUTHC from the LGA based on self-referral will also be identified and their data obtained.

Although the control arm participants do not have intervention provided in their LGA, they however get same workup, management and are navigated along the same pathway as the intervention arm participants once they present in OAUTHC for screening and diagnostic evaluation.

#### Program evaluation and outcome measures

The study timeframe is 2 years; however, a descriptive analysis will be carried out at 1.5 years to evaluate for the retention of study participants. A review will also be done at the end of year one to evaluate the progress of the research. Breast screening practices of the entire LGA will be re-assessed at the end of the first year in both the intervention and control LGAs. This will be compared with the baseline data already obtained before the commencement of the study to determine the impact of the intervention on breast cancer awareness and screening practices.

A full evaluation will be done at the end of 2 years. The following outcomes (Fig 4) have been defined a priori and will be used as metrics to assess the impact of the program.

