### Study design and setting

This project will be carried out in Osun State, Nigeria. Osun State, located in southwest Nigeria, comprises thirty Local Government Areas (LGAs). The study will use a randomized two group clinical trial design with one LGA serving as the intervention arm (Ife North LGA) and another LGA serving as the control arm (Ife East LGA). The two LGAs are located within the same state and consist of a homogenous group of people with similar demographics, culture, language, belief system and occupational pattern. Both Ife North and Ife East LGAs are made up of 10 wards each with an estimated population of 153,694 and 188,087 respectively based on the 2006 National census. This was projected to be 188,000 and 231,000 respectively in the year 2020 using annual population change of 1.6% for Nigeria between 2006 and 2022 [21]. The population projection assumes the same rate of growth for all LGAs within a state. Each ward is served by a dedicated primary healthcare centre (PHC). The two LGAs are similar in that they are in the same State with similar sociocultural characteristics and are within the catchment area of the Obafemi Awolowo University Teaching Hospitals Complex (OAUTHC), which is the referral centre for the two LGAs. Both LGAs will receive awareness and education, but only the intervention LGA will receive community-based breast evaluation and navigation. However, the control LGA located at coordinates; latitudes 7° 31′ N and 7° 34′ N and longitudes 4° 30′ E and 4° 34′ E has adequate access to screening and diagnostic evaluation because it is about 4 kilometers to the OAUTHC where radiological (including ultrasound, mammography, computerized tomography, and magnetic resonance imaging services), pathological and surgical specialty services for breast cancer screening and management are available. The intervention LGA located at coordinates; latitude 6° 58′ and 7° 35′ N and longitude 4° 22′ and 4° 37′ E is about 25 kilometers form OAUTHC. The referral center (OAUTHC) is in Ife central LGA and falls within the latitude 07° 30^′^ 0.0^″^ to 07° 31^′^ 6.71^″^ and within longitude 4° 33^′^ 0.0^″^ to 3° 34′ 30.64^″^.

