### Sample size calculation

#### Sample size of study participants

Three wards in Ife North (Ipetu II, Edunabon I and Moro) and two wards in Ife East (Modakeke I and Modakeke II) have been randomly selected to serve as the intervention and control arms respectively. The investigators anticipate the problem of contamination by potential study participants in the control arm who live in wards that share a boundary and are in proximity with the intervention arm. This was mitigated by excluding the wards in the control LGA located at the boundary region between the two LGAs before carrying out the random sampling to select the wards in the two LGAs. Okooko, Edunabon and Moro PHCs which serve Ipetu II (with screening population of about 2926), Edunabon I (with screening population of about 998) and Moro (with screening population of about 1876) wards respectively in Ife North LGA as well as Adeowo and Okebode PHCs which serve Modakeke I (with screening population of about 2251) and Modakeke II (with screening population of about 2249) wards respectively in Ife East LGA have been selected as the 5 PHCs where recruitment of women into the study will take place.

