#### Baseline survey

A survey of women in the 2 LGAs (n = 163, each) will be conducted to assess baseline knowledge of breast cancer, screening practices, and perceptions about breast cancer before awareness creation and intervention. The survey instrument (S3 File) has a total of 8 sections consisting of thirty-one items. The first seven sections of the survey instrument were adopted from the validated AWACAN tool [23] while the eighth section (containing ten questions on awareness of breast cancer screening modalities and practices) was developed for this study. The English version of the survey instrument was translated into Yoruba language (the local language spoken in the selected LGAs in South-west Nigeria) and back to English language to ensure comparability. This was performed by a linguistic expert in the Department of Linguistics and African Languages of Obafemi Awolowo University (OAU), Ile Ife, Osun State, Nigeria.

The selection of women for the survey will be done using multistage sampling from the district to the street. Within each street, household sampling will be by convenience sampling of any available woman 40 years and older. The number of women sampled from each district will be proportional to the fraction of the population the district represents. Each LGA will be re-assessed with the same survey instrument (S3 File) at the end of the first year.

The CHNs will also be evaluated to assess their level of knowledge about breast cancer before intervention. This will be done both quantitatively and through qualitative interviews to understand potential cultural nuances and perceptions about breast cancer that need to be factored into the execution of the project.

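### The year-one survey is read against baseline as the intervention's impact, although both LGAs get the awareness campaign and the LGA-wide sample dilutes any screening effect

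*Protocol article*

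**What the plan says.** Under Baseline survey, the protocol article sets the size and frame: "A survey of women in the 2 LGAs (n = 163, each) will be conducted". Districts are represented by population: "The number of women sampled from each district will be proportional to the fraction of the population the district represents". Within streets, "household sampling will be by convenience sampling of any available woman 40 years and older". The same instrument is used again in each LGA at the end of year one.

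Under Program evaluation and outcome measures, the repeat survey covers the whole LGA in both arms: "Breast screening practices of the entire LGA will be re-assessed at the end of the first year in both the intervention and control LGAs". Its stated use is: "This will be compared with the baseline data already obtained before the commencement of the study to determine the impact of the intervention", and the sentence goes on to name awareness and screening practices as what is affected.

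Two other sections bear on this. Study design and setting says "Both LGAs will receive awareness and education" and reserves community evaluation and navigation for the intervention LGA; Control arm confirms a similar awareness procedure there. Sample size of study participants names the randomly selected wards: "Three wards in Ife North (Ipetu II, Edunabon I and Moro) and two wards in Ife East (Modakeke I and Modakeke II". Recruitment takes place at the health centres serving those wards, and each LGA has 10 wards.

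**The concern.** The comparison that the text states is follow-up against baseline. Within one LGA, that change contains three things: the awareness campaign, which both arms receive; anything else that changed over the year; and whatever the community service added. Read as written, a rise in awareness would be credited to an intervention that did not differ between the arms in this respect, and a rise in reported screening would be credited in full to the service.

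The second problem is dilution. The survey represents the whole LGA, while the service operates from health centres serving 3 of 10 wards. A real rise among women near those centres is averaged with women for whom the service is more distant. If the remaining difference is small relative to what 163 women per LGA can detect, a flat result would say little about whether the service changed screening practice. The Introduction hypothesises greater screening participation and uptake, so the survey's reading matters even though it is not a listed outcome.

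**Working it through.** **Inputs from the protocol article.** 163 women per LGA per wave (Baseline survey). 10 wards per LGA; projected populations 188,000 and 231,000 (Study design and setting). 3 and 2 wards selected; screening populations 5,800 and 4,500; anticipated participation 70%, giving about 4,100 women (Sample size of study participants). 791 women in the intervention arm in year one (Sample size of cases). Alpha 0.05 (Statistical analyses). No derivation of 163 is given, so it cannot be reproduced.

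**Reproducing the plan's figure.** 0.70 × 5,800 = 4,060, which agrees with about 4,100. The ward counts add up: 2,926 + 998 + 1,876 = 5,800 and 2,251 + 2,249 = 4,500.

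**Share of the LGA in the selected wards (assumption).** With equal wards the share is 3/10. This is plausible: 5,800 / (0.3 × 188,000) = 10.3% and 4,500 / (0.2 × 231,000) = 9.7%, similar fractions in the two LGAs. The three wards are unequal among themselves, so I also take a range of 20–40%.

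- Respondents living in selected wards of Ife North: 0.3 × 163 ≈ 49 (range 33–65).
- Implied LGA total of women aged 40–70: 5,800 / 0.3 ≈ 19,333.
- Planned uptake, LGA-wide: 0.70 × 0.3 = 21 points (14–28).
- Observed year one: 791 / 5,800 = 13.6% of the selected wards' screening population, but 791 / 19,333 = 4.1 points LGA-wide (2.7–5.5). The 791 may include symptomatic women aged 30–39, so these are upper limits.

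**Power for the between-LGA difference in change.** Baseline screening b is not given; I assume 5%, 10% and 20%. Let x be the uptake above, falling equally on women already screened and not, so the rise is d = x(1 − b). With a flat control LGA, independent samples and no clustering:

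variance = [3b(1 − b) + (b + d)(1 − b − d)] / 163; power = P(|Z + d/SE| > 1.96).

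Worked case, b = 10%, x = 4.1%: d = 0.0368; variance = (0.270 + 0.1368 × 0.8632) / 163 = 0.00238; SE = 0.0488; d/SE = 0.75; power ≈ 12%.

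| Assumed baseline | Planned uptake (21 points) | Observed 791 (4.1 points) |
|---|---|---|
| 5% | 99% | 18% |
| 10% | 94% | 12% |
| 20% | 72% | 8% |

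Over the 20–40% range of ward share, power at the observed accrual is 11–28%, 8–17% and 6–11% for the three baselines. The change detectable with 80% power is about 12, 15 and 19 points.

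**Selected-ward subset within the same frame.** Taking about 49 women per wave in Ife North and 0.2 × 163 ≈ 33 in Ife East, and x = 13.6%, the same method gives about 35%, 22% and 13%. This is better than LGA-wide but still imprecise.

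**The case against.** Three objections have force.

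First, a reader might infer that the survey cannot show any effect on screening practice. The documents do not support that. Both LGAs are surveyed at both times, so all four cells of a difference in change are collected, and at the planned 70% uptake it would be detectable at low baseline rates. The Sample size of community health nurses section plans for that volume over a year; the smaller figure reflects year-one accrual, and the Discussion says that recruitment was initially slowed by COVID-19. What stands is that the contrast is not the one stated, and that at the accrual the article itself reports it would probably miss the effect.

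Second, a reader might infer that respondents outside the three wards had no access, and that moving the survey into the selected wards would solve the problem. Exclusion is by LGA and recruitment targets all eligible women, so women from other wards may attend. That does not rescue the 4.1 points, which already count all 791 against the whole LGA. As for moving the frame, a before-after calculation with 163 women per wave in the wards gives 96% power at a 5% baseline, against 28% LGA-wide. But that is the invalid contrast, and it needs a ward baseline that does not exist. With 163 per LGA at follow-up and ward baselines of about 49 and 33, the difference in change has about 58%, 34% and 19%. It would also break like-for-like comparison with a baseline already collected LGA-wide.

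Third, the survey is not a listed outcome, and participation has its own measure on a census denominator. That is correct and limits the consequence. It does not remove the impact claim attached to the survey. An LGA-wide frame also suits the description of a campaign that covers the LGA, which is a reason to keep it.

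**Conclusion.** The point holds in a limited form. For awareness, the attribution is wrong as stated: both LGAs receive the campaign, and a contrast between them could show at most what the community service adds to it. For screening practice, the before-after reading does not isolate the intervention. A between-LGA difference in change can remove change common to both LGAs, but the LGA-wide sample dilutes it to about 4 points at the reported year-one accrual, with power of about 18%, 12% and 8%. A null result there should not be read as no effect.

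The figures rest on equal ward shares, assumed baselines of 5–20%, a flat control LGA and no clustering. Convenience sampling within streets and an age range without an upper limit, against 40–70 for screening of asymptomatic women, add uncertainty that I have not quantified. With one LGA per arm, about 25 km and 4 km from the referral hospital, the contrast stays confounded with LGA whatever the sample. The stage-at-diagnosis comparison and the listed secondary outcomes are unaffected.

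**What to change.** In Program evaluation and outcome measures:

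- Define the impact on screening practice as the difference between the two LGAs in change from baseline, with its confidence interval, and say that a null result is uninformative if uptake is near the year-one level.
- Report awareness in each LGA as change under the campaign that both received, not as an effect of the intervention.

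In Baseline survey:

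- Keep the LGA-wide frame at year one so that the waves remain comparable.
- Record ward of residence and age on each year-one form.
- Report respondents aged 40–70 from the selected wards as a secondary analysis, provided that ward and age were recorded at baseline; the article does not show whether they were.

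The first two changes need wording only, and the rest adds items to the form but no interviews. The costs are low precision in the ward subset (about 49 and 33 women per wave, if wards are equal) and a contrast that remains confounded with LGA, which should be stated as a limitation.

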**Fig 4 pone.0284341.g004:**
[figure not shown]
Outcome measures in the control and intervention communities.

Primary outcome measures.

Stage at presentation: This will be determined using both clinical and radiological assessment to determine the TNM stage among those with histopathologically confirmed breast cancer. It is expected that the number of patients with late-stage disease may be high at the outset, but this is expected to reduce as screening progresses in the intervention arm. Therefore, besides the absolute number of cases per stage, the pattern of presentation over time will also be assessed to determine if there is a decline in the number of late-stage cases between the prevalence and incidence rounds of screening. Cases of breast cancer from the intervention and control arms will be tracked both at the PHCs and OAUTHC. The stage and pattern of presentation of cases from the two arms will be compared.

Secondary outcome measures.

Participation rate: This will be determined by calculating the percentage of women screened/evaluated of the total number of eligible women based on census data. A participation rate of 70% will be considered satisfactory in the intervention arm. The number of screened/evaluated women in the intervention and control arms will also be compared.Cancer detection rate (CDR): This refers to the number of histopathologically diagnosed cases of breast cancer per 1,000 evaluated populations in both screening and diagnostic groups. This will be compared between the control and intervention arms.Timeline from presentation to treatment: The time interval between presentation for breast evaluation and treatment in OAUTHC of the cases in the two arms will be compared.Retention rate: The retention rate refers to the number of women who return for repeat annual screening of the total initial number of women initially screened in the first year. A repeat screening within a year and a half will be considered acceptable for this two-year study. To ensure all accrued participants get their second screen, we will follow them up beyond the initial study period as needed.Abnormal call rate: This is defined as the number of women with abnormalities detected on iBE and/or CBE requiring further evaluation either by imaging with or without biopsy out of the total number of asymptomatic and symptomatic without an obvious lesion participating in the study. There are 2 groups of participants (diagnostic and screening) in each of the 2 arms (intervention and control). The screening group constitutes the asymptomatic participants while the diagnostic group constitutes the symptomatic participants. The interventions in this study include enhanced CBE (CBE + iBE), community-based diagnostic evaluation (with portable ultrasound and mobile mammography), and biopsy (if warranted). To evaluate which of CBE and enhanced CBE was of greatest value, another layer of analysis will be provided to address this question by comparing the concordance of the two with imaging which is the gold standard. This study also provides an additional opportunity to evaluate the iBE device.

A descriptive analysis of the data will be done at 1.5 years for the retention rate and abnormal call rate to inform our decision for future investigations. The rate of late-stage diagnosis will be estimated on a yearly basis. However, no stopping rules will be employed. This estimation will purely serve the purpose of detecting any difference in the annual trends of the stage of diagnosis over time between the intervention and control arms.

The initial findings for the subset of women who undergo a second round of screening will be examined to identify the stage of presentation in this group of women if diagnosed during the second round. Given in our setting ~80% of patients with breast cancer present in stages 3 and 4, we expect to see a trend toward earlier stage of presentation (stages 0, 1 and 2) in women undergoing repeat breast evaluation.

The 2-year study period is enough to generate adequate data to measure the participation rate and difference in stage at diagnosis between the study arms, as elaborated in the sample size calculation of the cancer cases. In addition, this study will provide a groundwork for exploring the difference in CDR between the 2 modalities (CBE and enhanced CBE) and the time to treatment, generating data to guide future studies in our population.

